### Potential further analyses

Depending on our initial exploratory findings, we will consider additional analyses. If we have sufficient cases of individuals with imaging features of NPH, we plan to undertake additional statistical analyses, such as Cox regression with time to mortality or dementia diagnosis as outcomes.

If we have sufficient cases, we will describe NPH imaging features in relation to outcomes such as hospitalisation, mortality, cognitive decline, and dementia diagnosis. We will describe hospitalisation profiles (eg. falls, surgery) in relation to NPH imaging features. We will look at factors associated with subsequent diagnosis compared to no diagnosis among people with imaging features of NPH.

If, as expected, we find few cases of NPH, we will define NPH ‘imaging cases’ based on the presence of suggestive imaging features and their relationship with NPH diagnosis, and consider a nested case-control study. We will assess for differences in risk factors, demographics, and clinical covariates (see
Table 2) between cases and controls using logistic or categorical regression.

We plan to test our measures in low-field MRI
^
72
^, and we will consider comparing our findings in other datasets
^
73
^.

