### Memory services

No study has so far explored the role of memory services in assessing people with possible NPH in England, though these are an important source of referrals for NPH clinics
^
41
^. To the best of our knowledge, only one study has examined imaging features of NPH in a memory clinic population
^
38
^.

Electronic health record (EHR) studies of NPH are limited by the possibility of false negatives in recorded diagnoses, due to suspected under-diagnosis of NPH
^
12,
22
^. There is a need to further our understanding of clinical and radiological features suggestive of NPH in clinical populations. In addition, we lack normative data regarding NPH imaging features in clinical populations, which is key when considering the development of screening tools for this condition.

We therefore propose the first study of NPH and its clinical and radiological features in memory clinics in the UK. Little is known about this topic and this study will provide an initial exploration of a neglected area of research. NPH is a rare outcome, with an expected prevalence of 1% in memory services
^
38
^. Due to the uncertainty surrounding recorded diagnosis of NPH, and the frequent co-occurrence of NPH with other neurodegenerative conditions
^
42
^, this study will also examine for the first time whether imaging features of NPH are independent predictors of outcomes, and whether they are associated with prognosis in other diagnoses such as AD and Parkinson’s disease.

Untreated NPH is associated with a higher risk of dementia and death than the general population
^
43
^. If CA or other imaging markers are validated as a reliable measure for this population, these could be developed as automated decision-support tools for NPH, with the potential to benefit both individuals and healthcare systems. Though shunting is not appropriate or effective for all, it could alleviate symptoms and reduce long term costs in a potentially large number of people with cognitive decline. The possibility to prolong independence and potentially delay dementia onset at a time when global dementia cases are unprecedentedly high and set to increase
^
44
^, makes study of NPH a priority.

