### Study design

We will assemble a retrospective cohort study using SLaM’s CRIS data platform. The study population will be all people aged 60 years and above with at least one referral to memory services recorded over the study period 2007–2024. We expect at least 20,000 participants in this cohort. We will extract relevant anonymised retrospective patient data from CRIS for the entirety of the cohort and specify the data extraction date. We will examine CRIS data and use linkage data to HES, ONS, and imaging data.

A subset of this cohort will have linked T1-w, T2-w, and FLAIR brain MRI scans that have been collected as part of routine clinical care over the period 2008–2021. We expect to have at least 5,000 people in this sample, based on the number of scans currently available, however the sample size is subject to change as these datasets are live.

*Inclusion criteria:*

Aged at least 60 years at time of memory clinic referralReferral to memory services, recorded in CRISPeople who are referred but do not attend a review will be included and compared with those who do attend, though they may have limited data

*Exclusion criteria:*

Nil

*Cohort entry date:*

Date of referral to memory service

*Exit from cohort:* Censored at minimum of

DeathIncident NPH diagnosisEnd of study period

*Covariate assessment window:*

Anytime prior to cohort entry date up to three months after date of first face-to-face or virtual review in memory clinic, inclusive

*Primary outcome:* ICD10 code G91.2 recorded in CRIS
*or* HES
*or* ONS,
*or* context-confirmed NPH recorded in CRIS

*Possible secondary outcomes:*

MortalityHospitalisation profileDementia diagnosisCognitive trajectorySymptoms of NPH (eg. falls)

*Exposures:*

CA in degreesVentricular volume in mm
^3^
White matter hyperintensities (WMH) volumesOther brain measures to be determined (TBD)

*Possible covariates:*

AgeSexEthnicityIMDRisk factors for NPHCognitionHealth of the Nation Outcome Score (HoNOS)

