### Diagnostic accuracy of CA

We will compare mean or median CA between people with a diagnosis of NPH and other diagnoses, such as dementia and its subtypes, in particular AD, using a two-sample t-test or Mann-Whitney U test.

We will analyse the association between NPH imaging features and NPH diagnosis using logistic regression. If we have sufficient numbers, we will consider using area under the curve (AUC) analysis, and Cox regression for time-to-event analysis. We will consider penalised Cox regression if the number of outcome events is small, as we expect.

If we have enough cases, we will calculate the sensitivity, specificity, positive, and negative predictive values for identifying recorded NPH in this population using CA. Estimated numbers for this are in
Table 3.

**Table 3. T3:** Expected values of cases of NPH picked up on screening in CRIS (based on initial searches undertaken in March 2022). Based on total population of 5,000 individual patient scans and an expected prevalence of approximately 1% of dementia cases
^
71
^. Figures are based on previous sensitivity (97%) and specificity (88%) measures using a cut-off of <90 degrees
^
31
^.

True iNPH cases				
Callosal angle <90		+	-	Totals
	+	49	582	631
	-	1	4268	4269
	Totals	50	4850	5000

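### Subsequent NPH diagnosis is framed as ever versus never over unequal follow-up, so early deaths and late scans would count as undiagnosed

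*Protocol article*

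**What the plan says.** The Abstract hypothesises that imaging features will predict a future diagnosis of NPH. Three sections of the protocol's Methods bear on how that would be analysed.

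- **Potential further analyses.** "We will look at factors associated with subsequent diagnosis compared to no diagnosis among people with imaging features of NPH". No model, time origin, window or treatment of death is given. The section is conditional: "Depending on our initial exploratory findings, we will consider additional analyses". It names "Cox regression with time to mortality or dementia diagnosis as outcomes"; NPH diagnosis is not among those outcomes. For the optional nested case-control study, differences would be assessed "between cases and controls using logistic or categorical regression".
- **Diagnostic accuracy of CA.** "We will analyse the association between NPH imaging features and NPH diagnosis using logistic regression". This is unconditional. Then: "If we have sufficient numbers, we will consider using area under the curve (AUC) analysis, and Cox regression for time-to-event analysis". The next sentence adds that penalised Cox regression will be considered if events are few, which the authors expect.
- **Study design.** Cohort entry is the referral date. Exit is the earliest of death, incident NPH diagnosis and end of study. The study period is 2007–2024. On imaging: "A subset of this cohort will have linked T1-w, T2-w, and FLAIR brain MRI scans that have been collected as part of routine clinical care", with scans dated 2008–2021.

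**The concern.** The question is prospective: who, among people with suggestive imaging, is later diagnosed? An ever/never outcome answers it cleanly only if everyone is observed for the same time and few die first. Neither condition holds here. Someone scanned in 2021 has about 3 years in which to be diagnosed, and someone scanned in 2008 has 16 or more. People who die soon after the scan have less still. All of them would enter the no-diagnosis group as if fully observed, and the censoring rule in Study design would go unused.

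At stake is the reading of missed NPH, of which the protocol promises a first estimate under Strengths and limitations. Age, deprivation and vascular disease are listed covariates or risk factors and plausibly affect survival. A difference in survival could be reported as a difference in how readily a group is diagnosed.

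**Working it through.** **Figures in the protocol.** It gives no figure for this analysis. Its only power calculation (5 per group for a difference in mean CA) concerns another question.

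**Inputs from the protocol.** Scans 2008–2021 and study end 2024 give potential follow-up from 2024 − 2021 = 3 years to 2024 − 2008 = 16 years, or about 17 counting from the start of 2008 to the end of 2024.

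**Assumed inputs.** The documents give no diagnosis or death rates. I take constant hazards, a diagnosis hazard h of 0.01–0.10 a year, a death hazard m of 0.10 (reference) or 0.20 (factor present) a year, and follow-up T uniform from 3 to 16 or 17 years.

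**Formula.** The probability of being diagnosed by T, with death competing, is

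P(T) = h/(h+m) × [1 − exp(−(h+m)T)].

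For T uniform on 3 to 16, with k = h+m, the average is

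(h/k) × {1 − [exp(−3k) − exp(−16k)]/(13k)}.

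**Step 1: a factor that doubles mortality and does not affect the diagnosis rate.** With h = 0.02:

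- m = 0.10, k = 0.12: (0.02/0.12) × (1 − 0.3532) = 0.1078
- m = 0.20, k = 0.22: (0.02/0.22) × (1 − 0.1704) = 0.0754
- Odds ratio = (0.0754/0.9246)/(0.1078/0.8922) = 0.68; the true rate ratio is 1

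| h per year | OR, follow-up 3–16 y | OR, follow-up 3–17 y |
|---|---|---|
| 0.01 | 0.68 | 0.67 |
| 0.03 | 0.67 | 0.66 |
| 0.10 | 0.64 | 0.63 |

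With the reference death hazard varied over 0.05–0.20, again doubled, and h from 0.01 to 0.05 (follow-up 3–16 years), the range is 0.57–0.79. A simulation with h = 0.02 and m = 0.10 versus 0.20 gave a logistic odds ratio of 0.70 against a person-time rate ratio of 1.03.

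**Step 2: scan date alone.** With equal hazards (h = 0.02, m = 0.10), P(3) = 0.050 and P(16) = 0.142. The odds ratio for 3 versus 16 years is 0.32. This distorts a factor only if that factor is associated with scan year.

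**Step 3: diagnoses only in the first year after the scan.** With h from 0.02 to 0.10 and the death hazard doubled from 0.05, 0.10 or 0.20, the odds ratio is 0.90–0.98. The distortion is then small.

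**Step 4: a factor that also raises the diagnosis rate.** With h = 0.02, m doubled from 0.10 and follow-up 3–16 years, raising the diagnosis hazard 1.25-, 1.5- or 2-fold gives odds ratios of 0.85, 1.02 and 1.37. The estimate is pulled down in each case, but it need not fall below 1.

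**The case against.** The strongest reply is that the protocol never commits to a binary model here. The sentence under Potential further analyses names no method, Study design sets out a time-to-event structure with censoring at death, and Diagnostic accuracy of CA contemplates Cox for ample events and penalised Cox for few. The Abstract also mentions survival analysis. This stands in part: it is wrong to say that the authors overlooked survival methods or ruled them out for small numbers. But nothing attaches them to this contrast, and Cox is only to be considered, whereas logistic regression will be done.

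Logistic regression is also conventional beside AUC, sensitivity and specificity. That stands for concurrent diagnosis; it does not carry over to future diagnosis.

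A further reply is that a person who dies undiagnosed really was never diagnosed, so the ever/never proportion is a legitimate quantity. It is, and it is the cumulative incidence with death competing. It needs a stated horizon, and it should be shown next to the diagnosis rate so that differences in survival are not read as differences in clinical recognition.

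Two stronger readings are tempting and should be resisted. A reader might infer that anything shortening survival will look like a cause of missed NPH; step 4 shows otherwise. A reader might also infer that the CA association is biased towards the null, because the protocol says "Untreated NPH is associated with a higher risk of dementia and death than the general population". That comparison is with the general population. It does not show that people with a narrow CA die sooner than other memory-clinic patients, many of whom have dementia. Neither the size nor the direction of any bias for CA can be established from the documents.

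**Conclusion.** The point holds in a limited form. The contrast is worded as ever/never, the one firm model for NPH diagnosis is logistic, and post-scan follow-up varies about fivefold in an older cohort. Run that way, a factor that shortens survival without altering the diagnosis rate can appear associated with going undiagnosed. The size rests entirely on assumed rates and on how soon after the scan diagnosis occurs: appreciable if diagnoses are spread over follow-up, slight if they cluster in the first year. Severity is low to moderate, since the analysis is conditional and exploratory and carries no primary result.

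**What to change.** For the future-diagnosis hypothesis and for the contrast under Potential further analyses:

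1. Exclude diagnoses made before the scan, or report them separately.
2. Start time at the scan date rather than at referral.
3. Make the Cox or penalised Cox model already contemplated the stated analysis: cause-specific, censoring at death and study end.
4. Show the cumulative incidence of diagnosis with death as a competing event.

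Alternatively, keep logistic regression but restrict it to a fixed post-scan window open to every scan, for example 12 months, and report deaths within it. With m = 0.10 versus 0.20 and h = 0.02, the 12-month probabilities are 0.01885 and 0.01795, an odds ratio of 0.95, so little distortion remains.

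Logistic regression and AUC can stay for concurrent diagnosis under Diagnostic accuracy of CA.

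The cost is a few sentences and slightly more analysis. Scan and death dates are in the planned extraction, and the cohort exit rule already requires a diagnosis date. No extra events are needed to fit the model, because logistic and Cox regression both draw on the same diagnoses.

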### Sample size and power calculation

In initial feasibility searches carried out in March 2022, keyword search for ‘hydrocephalus’, excluding ‘no hydrocephalus’, yielded 896 records. Validation of a subsample gave a total number of 251 cases of potential NPH, based on examination of the context. Feasibility counts show 136 patients aged >50 with a shunt in CRIS.

Using STATA V16.1, we calculated the sample size required to test for a difference in means using a two-sample t-test. Measures were based on the following expected means and standard deviations (SD) for CA
^
31
^:

NPH = 66 (SD= 14)

AD = 104 (SD= 15)

To test for a difference with 90% power and an alpha level of 0.05, we calculated a required sample size of 10, with 5 in each group. Based on initial feasibility counts, we should have ample cases in our sample to estimate this expected difference in mean CA. With a conservative estimate of 49 cases of NPH, we should have 90% power to detect a minimum difference of 10° in mean between NPH and AD groups.

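### Sampling controls in the imaging-case fallback discards scanned people whose data are already held, with no saving stated; the regression should use all of them

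*Protocol article*

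**What the plan says.** The fallback is in the Protocol article, Potential further analyses. Its trigger is a small number of NPH cases, which the authors expect. Imaging cases are then to be defined "based on the presence of suggestive imaging features and their relationship with NPH diagnosis, and consider a nested case-control study". Risk factors, demographics and clinical covariates are to be compared "between cases and controls using logistic or categorical regression". The protocol fixes no cut-off, control definition, matching or case-to-control ratio.

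Three other places bear on this:

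- Study design, on clinical data: "We will extract relevant anonymised retrospective patient data from CRIS for the entirety of the cohort". On the imaging subset: "We expect to have at least 5,000 people in this sample".
- Table 2 takes most risk factors from structured codes, drug searches and natural-language tools, and most imaging measures from automated pipelines.
- Descriptive analyses already commits to treating the imaging measures as both continuous and categorical, and to describing how they vary by demographics, covariates and risk factors. It names no regression of imaging measures on risk factors.

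Strengths and limitations credits a possible nested case-control study with avoiding recall bias, because the records were made at the time of care.

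**The concern.** A nested case-control sample earns its loss of precision when exposure data are expensive to obtain for everyone. Here they are extracted electronically for the full cohort, so each unsampled non-case is a person whose data are held and not used. The recall-bias argument does not support sampling, because the full scanned cohort has the same contemporaneous records.

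The only regression that the protocol names for risk factors against imaging status sits on this dichotomised and possibly sampled data. At stake are the questions on ethnicity, deprivation, schizophrenia, diabetes and similar factors. The protocol presents the cohort's diversity as a major strength, and socio-demographic questions were added after patient and public input. An underpowered comparison could be read as absence of association.

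**Working it through.** **The plan's own figures.** The sample size section sets out to "test for a difference in means using a two-sample t-test", using CA 66 (SD 14) in NPH and 104 (SD 15) in AD, and reports: "To test for a difference with 90% power and an alpha level of 0.05, we calculated a required sample size of 10". With a two-sided noncentral t calculation, 4 per group gives 86.7% power and 5 per group gives 95.0%, so 5 per group is right. It also states: "With a conservative estimate of 49 cases of NPH, we should have 90% power to detect a minimum difference of 10" degrees. Taking 49 against 49, power at 10 degrees is 92.2%, so that holds too. Neither figure concerns the fallback, which has none.

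**Inputs.** From the protocol: 5,000 scans; SD 15; means 66 and 104; and, in Table 3, 88% specificity "using a cut-off of <90 degrees". Table 3's cells sum to 4,900, not 5,000 (49 + 582 + 1 + 4,268). Its flagged share is 631/5,000 = 12.6%, or 631/4,900 = 12.9%, which makes no difference here. Assumed, because the protocol gives no values: two-sided alpha 0.05, risk factor held by 20%, ratios 1:1 to 1:4, and the effect sizes below.

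**Step 1: information kept by sampling alone.** If a share p are cases and k controls are drawn per case, the fraction of the dichotomised information kept is about k / [(1 + k)(1 − p)].

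- p = 12.6%: 1/(2 × 0.874) = 57% at 1:1; 4/(5 × 0.874) = 92% at 1:4.
- p = 1%: 1/(2 × 0.99) = 51% at 1:1; 4/(5 × 0.99) = 81% at 1:4.

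The loss is therefore 43–49% at 1:1 and 8–19% at 1:4.

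**Step 2: a factor that shifts the whole CA distribution by 1.5 degrees.** Take mean 107.6 in the unexposed, so that 12% fall below 90.

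- Continuous CA, all scans: SE = 15 × √(1/1,000 + 1/4,000) = 0.530; 1.5/0.530 = 2.83; power Φ(2.83 − 1.96) = 81%.
- Cut at 90: Φ(−17.6/15) = 12.0% of unexposed and Φ(−16.1/15) = 14.2% of exposed are cases. Expected counts are 141.6 exposed and 481.3 unexposed cases, and 858.4 exposed and 3,518.7 unexposed non-cases. Log OR = 0.187.
- All non-cases: SE = √(1/141.6 + 1/481.3 + 1/858.4 + 1/3,518.7) = 0.103; ratio 1.82; power 44%.
- With non-cases thinned: 1:1, SE 0.139, power 27%; 1:2, SE 0.119, power 35%; 1:4, SE 0.108, power 41%.

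With the protocol's AD mean of 104, the figures are 81% continuous, 51% cut in all scans, and 33%, 43% and 50% with 1:1, 1:2 and 1:4 sampling.

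**Step 3: a factor that acts only through a latent NPH group.** Assume 2% latent prevalence, OR 3 and a cut at 70.

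- Solving 0.8p0 + 0.2p1 = 0.02 with OR 3 gives p0 = 1.45% and p1 = 4.22%.
- Shares below 70: Φ(4/14) = 61.2% of NPH and Φ(−34/15) = 1.17% of others. Cases are then 3.70% of exposed and 2.04% of unexposed, about 119 in all. Log OR = 0.614.
- All non-cases: SE 0.201, power 86%. 1:1: SE 0.304, power 52%. 1:4: SE 0.229, power 76%.
- Linear CA: mean difference 38 × (0.0422 − 0.0145) = 1.05; SE 0.562; power 47%.

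Simulation and other calculations of this scenario give 82–85%, 52–53% and 74–77% for the cut, and 43–47% for linear CA. About 85%, 52% and 77% is a fair summary, good to roughly three points. With 50% exposure and a cut at 75, the pattern is the same: 71% with all non-cases, 44% at 1:1, 63% at 1:4, and 38% for linear CA.

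**Reading.** Control sampling loses power in both models. The cut loses power in step 2 and gains it in step 3.

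**The case against.** The strongest reply is that nothing is fixed. The nested case-control study is only to be considered, and only the design's name implies sampling. The ratios and cut-offs above are assumptions, and imaging cases may rest on several features. At 1:4 the loss in step 2 is three points. This stands as a limit on size. It does not supply a reason to sample.

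A reader might infer that the plan throws away most of its power by dichotomising. The documents do not support that. Descriptive analyses already plans continuous measures and their variation by risk factor in the scanned sample, unconditionally, and the fallback comes on top. An article may also leave the choice of model to a fuller document, so the missing model name is not itself a fault.

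Nor does it follow that linear regression of CA should replace the imaging-case analysis. If a factor acts only in a small NPH subgroup, a strict cut beats the mean comparison (step 3). Mean CA in all patients also answers a different question from who looks like NPH, which matters for the stated aim of estimating missed NPH.

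Finally, it would be too strong to say that every scanned person has all covariates. The protocol expects missing data, excludes poor scans, allows for measurement failure and has no language-processing tool for gait. Sampling controls repairs none of these. Manual note review could justify sampling for particular items, but the protocol does not give that reason.

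**Conclusion.** The point holds for control sampling. The protocol extracts clinical data for the whole cohort, measures imaging largely by automated tools, and states no saving from sampling. The loss appears under both effect models: 44% to 27% (1:1) or 41% (1:4) for a general CA shift, and about 85% to 52% or 77% for an effect confined to the NPH tail. It is material at 1:1 and modest at 1:4. All these figures rest on the assumed exposure, effect sizes, cut-offs and ratios.

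On dichotomising, the conclusion is conditional. It costs a good deal if a factor shifts CA generally (81% against 44%) and can help if the factor acts only in the tail. Since the documents do not settle which applies, both analyses belong in the risk-factor work. This is a change worth making to an exploratory analysis, not a flaw in the study's main aims.

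**What to change.** In Potential further analyses, replace the nested case-control sample by logistic regression of imaging-case status in all scanned people with usable measurements, with all imaging-negative people as the comparison group. Keep control sampling only for items that need manual note review, and say which those are.

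Alongside it, regress the continuous imaging measures on the Table 2 risk factors in all scanned people, with adjustment chosen from the planned causal diagrams. Allow for effects confined to the tail, for example by quantile regression. This carries the continuous approach of Descriptive analyses into the risk-factor regression.

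The cost is a wording change and slightly more analysis work. No new extraction or measurement is needed.
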